#### Recruitment {15}

Case managers from the job centers can refer adult Danish-speaking citizens on sick leave from either work or unemployment to a psychiatric assessment if either the case manager, the citizen, or the individual’s general practitioner (GP) suspects a mental health condition to have caused the sick leave. The referral and assessment are voluntary. The results of the psychiatric assessment will be used in the treatment plan if the participant is allocated to treatment in IBBIS-II. The results of the assessment will be shared with the individual’s GP and the job center. The psychiatric assessment is based on three sources of information about the participant:Personal interview conducted by a care manager/psychologist and supervised by a psychiatrist, guided by the following instruments:Mini-International Neuropsychiatric Interview (MINI), modified to also including stress and burnout [9]Standardized Assessment of Personality – Abbreviated Scale (SAPAS) [11]Level of Personality Functioning Scale – Brief Form (LPFS-BF) [12]Common Mental Disorders Questionnaire (CMSQ) (questions 1–19) [13]Attention-deficit/hyperactivity disorder symptom checklist for adults (Adult ADHD Self Report Scale version 1.1) [14]If dementia is suspected, Mini-Mental State Examination (MMSE)Self-assessed symptoms, e.g., the Four-Dimensional Symptom Questionnaire (4DSQ) [15]GP’s sick leave note

Assessors are IBBIS-II team members who are specially trained to use the abovementioned instruments. Trial eligibility will be evaluated after the psychiatric assessment, and subsequently, assessment data will constitute the baseline data (see Table 1). The assessment process should not take more than 2 weeks but can be prolonged if one or more of the three types of information are missing.

#### Concealment mechanism {16b}

To ensure concealment, the randomization schedule is stored away from the research team, and the block sizes are not disclosed.

#### Implementation {16c}

Administrative personnel in the IBBIS-II team perform the online randomization, and the IBBIS-II team leader will assign the participant to interventions and professionals.

### Assignment of interventions: blinding

#### Who will be blinded {17a}

Participants in the trial and the personnel applying the intervention cannot be blinded to the group allocation, whereas those who refer participants, data collectors, and evaluators will be blinded both to the allocation sequence and block size of the randomization, to ensure that they cannot determine which group is the intervention group. During the analysis phase, the groups will be assigned other names, e.g., “X” and “Y,” and the evaluator will only have access to information about the group assignment after the analysis phase has been conducted and the conclusion drawn.

#### Procedure for unblinding if needed {17b}

We do not anticipate any requirement for unblinding because all the included follow-up outcomes are register-based meaning that there are no assessment procedures where unblinding can occur. The computer-generated allocation sequence will be kept unknown to the data analysts until all analyses are performed and conclusions are drawn.

### Data collection and management

#### Plans for assessment and collection of outcomes {18a}

The participants will be followed up at 6 and 12 months using register-based data. The primary, secondary, and explorative outcomes are presented in Table 1. The primary outcome is RTW measured by time to RTW from baseline until 12 months after baseline using register-based employment data (DREAM database). Time to RTW is defined as a minimum of 4 weeks of continuous work without receiving sickness benefits. The secondary outcome is the proportion of unsupported competitive employment at 12 months follow-up using DREAM data. Explorative outcomes include measures of labor market attachment using DREAM data and electronic income data, as well as primary and secondary healthcare using health care data from the National Danish registers (Table 1). The Four-Dimensional Symptom Questionnaire (4DSQ) is a 50-item questionnaire designed to assess self-reported common psychological symptoms in the last week and has a special focus on distinguishing general distress from depression, anxiety, and somatization [15]. The Work and Social Adjustment Scale (WSAS) [16] is a simple, reliable, five-item scale that measures functional impairment related to an identified problem, which is defined in this trial as psychological symptoms. The Karolinska Exhaustion Scale (KES) 26-item version measures the degree of exhaustion disorder and the four interrelated dimensions of exhaustion disorder according to the Swedish National Board of Health and Welfare: lack of recovery, cognitive exhaustion, somatic symptoms, and emotional distress [17]. The Level of Personality Functioning Scale – Brief Form (LPFS-BF) 2.0 measures impairment in personality functioning [12]. The Common Mental Disorders Questionnaire (CMDQ), questions 1–19, is covering symptoms and signs commonly associated with somatoform disorders and worries about health validated as a diagnostic aid in primary care settings [13]. The Sheehan Disability Scale (SDS) measures functional impairment in three inter-related domains: work/school, social life, and family life [18, 19]. Return to work self-efficacy (RTW-SE) is an 11-item measure for self-efficacy beliefs regarding return to work where respondents are asked to respond to statements about their jobs, imagining that they would start working tomorrow in their present emotional state [20]. The 17 items University of Washington Self-Efficacy Scale (UW-SES) measure self-efficacy and is validated across diagnostic conditions [21]. The Flanagan QOLS is a 16-item instrument that measures 5 conceptual domains of quality of life: material and physical well-being; relationships with other people; social, community, and civic activities; personal development and fulfillment; recreation; and independence [22]. The EQ-5D-5L is a measure of health status in five domains: mobility, self-care, usual activities, pain/discomfort, and anxiety/depression and also includes a visual analog scale from 0 (worst imaginable health status) to 100 (best imaginable health status) [23].

#### Plans to promote participant retention and complete follow-up {18b}

All analyses are based on the intention-to-treat principle, and because all outcome measures are exclusively based on register-based data, there will be near to complete follow-up data. Only if a participant wants to discontinue both the intervention and the experiment the data will not be used.

If participants want to discontinue the intervention, there are two options:They discontinue the intervention, but not the experiment, i.e., data can be used in the research project.They discontinue both the intervention and the experiment and data cannot be used and must be deleted.

#### Data management {19}

The data management is handled by the private company Deloitte, Department of Artificial Intelligence & Data. All electronic data (self-assessment, interview, and register data) are stored on secured servers at closed networks, and access to data is logged through a unique login for an assigned list of IBBIS-II personnel. Physical data material (case report forms with selected interview data) is stored in locked spaces in locked facilities. Transfer of electronic data between staff members and other approved data managing institutions is carried out using only tunnel encrypted email or encrypted USB sticks (Table 2).

**Table 2 Tab2:** Enrollment and data collection

	Baseline	Randomization	6-month follow-up	12-month follow-up
Informed consent	X			
Case report form	X			
Randomization database		X		
Self-assessment data	X			
Register data			X	X

#### Confidentiality {27}

All data will be stored following the European General Data Protection Regulation, as well as national guidelines. Personal information on participants is entered directly into an electronic case report form administered by Deloitte. Only data on participants who have consented to participate in the trial will be stored. At the termination of the trial, data will be transferred to the national archives in accordance with Danish legislation.

#### Plans for collection, laboratory evaluation, and storage of biological specimens for genetic or molecular analysis in this trial/future use {33}

This trial does not involve collecting biological specimens for storage.

## Statistical methods

### Statistical methods for primary and secondary outcomes {20a}

The primary aim is to test whether there is a difference in time to RTW, between the two groups, during the 12-month follow-up period. Since the primary outcome is analyzed exclusively with register data, data is expected to be complete. Kaplan-Meier survival curves will be presented, and the differences between the two intervention groups will be analyzed with a Cox proportional hazards regression. The treatment effect estimates are presented with a hazard ratio (HR) at 95% confidence intervals (CI). Also, Cox regression analysis will be used to analyze the secondary outcome, time from RTW, to any possible new period of sick leave of more than 4 weeks in the 12-month follow-up period.

All continuous outcome measures, including the number of weeks at work and wage income during the follow-up period, will be analyzed by linear regression and presented with mean differences and 95% CI. If data is skewed, a non-parametric test will be used. The dichotomous outcome, employment at one point in the follow-up period, will be analyzed with logistic regression and presented with percentages, odds ratio, and 95% confidence interval. All models will be adjusted for the stratification variables, as well as previous work history and history of social benefits, where a bivariate duration model will be used (number of days in employment or public benefit 5 years before baseline). All analyses will be conducted separately for the two independent randomizations associated with the pilot study and main trial, respectively, as well as collapsed. Subgroup analyses will also be performed (see additional analyses). Only the primary and secondary research questions are considered confirmatory. All other endpoints are considered exploratory, and no adjusting for multiple testing will be introduced.

### Interim analyses {21b}

No interim analyses will be performed in the trial.

### Methods for additional analyses (e.g., subgroup analyses) {20b}

All outcomes are analyzed in subgroup analyses consisting of the following:Diagnosis subgroups: anxiety, depression, stress, and functional and personality disorder. Participants from Western and Eastern DenmarkSelf-efficacy: participants with low (≤ 8) or high (> 8) baseline self-efficacy measured by the UW-SESPeople on sick leave from work or unemploymentBenefits received after sickness benefit, measured at 12 months follow-up and stratified by unemployment benefits, subsidized “flexjobs,” work subsidy in private and public companies, cash benefits, and SU (the Danish students’ Grants and Loans Scheme)

Moreover, the participants from the pilot phase will be included in the additional sensitivity analysis on the included outcomes.

An elaborate data analysis plan will be prepared before the analytic phase and will be uploaded to ClinicalTrials.gov.

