#### Intervention description {11a}

The IBBIS-II service is thoroughly described in the manual and educational material. The service is briefly described below. The IBBIS-II service is delivered by two teams—one in Copenhagen and one in Aarhus. Each team has a team leader and consists of the following:Employment specialists who operate as caseworkers and are employed by job centersCare managers consisting of nurses, occupational therapists, physiotherapists, etc. with experience in mental health care and a minimum of 1 year of training in cognitive behavioral therapyOther healthcare professionals (psychologists, psychiatrists, specialists in social medicine, physiotherapists, and instructors in mindfulness-based stress reduction)

Healthcare professionals are employed by the two collaborating regions, and employment specialists are employed by the job centers in the two municipalities. Care managers have a maximum momentary caseload of 25, and employment specialists have a maximum momentary caseload of 30.

The entire staff has received training in the IBBIS-II service prior to the initiation of the study, and the employment specialists and care managers receive ongoing supervision.

The IBBIS-II services have the following core elements:AssessmentAll participants referred to the service receive a mental health assessment.Planned integrated serviceThe participant has the same employment specialists and care manager throughout the intervention.A joint plan is made with shared decisions between the participant, the employment specialist, and the care manager.There is a focus on disclosure (openness about illness) and involvement of relatives and significant others.Vocational rehabilitationFocus on RTW with ongoing assessment of job goals, competencies, and need of support.Participants receive help in contacting existing employers (employed) and potential employers (unemployed).Unemployed participants are offered an individualized job search effort.The focus is on competitive jobs within the community.The treatmentIs based on stepped care and uses structured treatment guidelines. The stepped care includes the following:i.Psychoeducationii.Work-related cognitive behavioral therapy for depression and anxiety disorders and special stress interventions for stress and stress-related disordersiii.Psychotherapy, physiotherapy, and medical treatmentOngoing supportWhen the participant has obtained work the team continues to offer support.

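### One planned subgroup is defined by the benefit received at 12 months, after randomisation, so the arms are not comparable within it and its effect estimates have no causal meaning

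*Protocol article*

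**What the plan says.** Under Methods for additional analyses {20b}, the protocol article introduces its list with "All outcomes are analyzed in subgroup analyses consisting of the following". The list holds diagnosis, region, baseline self-efficacy, sick leave from work or from unemployment, and finally benefits "received after sickness benefit, measured at 12 months follow-up and stratified by unemployment benefits", continuing with "subsidized “flexjobs,” work subsidy in private and public companies, cash benefits, and SU".

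The outcomes to be compared within these groups include:

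- Primary, in Plans for assessment and collection of outcomes {18a}: "The primary outcome is RTW measured by time to RTW from baseline until 12 months after baseline". The event is defined there as follows: "Time to RTW is defined as a minimum of 4 weeks of continuous work without receiving sickness benefits".
- Secondary, in the same section: "The secondary outcome is the proportion of unsupported competitive employment at 12 months follow-up using DREAM data".

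The Outcomes section {12} takes social benefit data from DREAM, the register that also supplies both of these outcomes. Nothing in the article treats the benefit item as a descriptive outcome or adds a caution about a subgroup formed after randomisation.

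**The concern.** A subgroup comparison is protected by randomisation only if the subgroup factor could not have been influenced by treatment. Diagnosis, region and labour market status are randomisation strata (Sequence generation {16a}), and self-efficacy is explicitly the baseline value. Benefit type at 12 months differs from all of these. IBBIS-II aims at faster return to work and better job retention (Objectives {7}), and its support carries on after work is found: once the "participant has obtained work the team continues to offer support". Whether a participant is on a benefit at 12 months, and on which one, is therefore a result of treatment.

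Two consequences follow. Within a benefit stratum the two arms are different selections of people, so a hazard ratio or odds ratio there mixes any treatment effect with that selection. The secondary outcome is also read at the same time point and from the same register as the stratifying variable, so in several strata the stratum largely fixes the outcome. A reader could take a number from these strata as showing for whom the intervention works or fails, when it cannot show that.

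**Working it through.** **1. The protocol's own figure.** Sample size {14} plans the secondary outcome at 60% v 75% with 450 per arm, and gives power 0.8 at 151 per group. A two-proportion test (pooled variance, two-sided 0.05, 1:1) gives power 0.798 at 151 per group and 0.998 at 450 per group. The stated figures reproduce, so 60% and 75% can be used as the protocol's working rates. I read 60% as SAU and 75% as IBBIS-II.

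**2. Size of the pool from which most benefit strata are drawn.** Not in employment at 12 months:

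- SAU: 450 × (1 − 0.60) = 180
- IBBIS-II: 450 × (1 − 0.75) = 112.5, about 112
- Ratio: 180 / 112.5 = 1.6

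Randomisation was 1:1. The 1.6:1 split comes entirely from the assumed treatment effect.

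**3. Who is left in that pool.** Assume one standard-normal baseline prognostic factor, balanced at randomisation, acting on 12-month employment through a logistic model with the marginal rates held at 60% and 75%. The strength of the factor is an assumption, so a range is shown.

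| Log-odds per SD | Mean among not employed, SAU | Mean among not employed, IBBIS-II | Difference (SD) |
|---|---|---|---|
| 0.5 | −0.283 | −0.356 | −0.07 |
| 1.0 | −0.498 | −0.638 | −0.14 |
| 1.5 | −0.639 | −0.829 | −0.19 |

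The better the intervention works, the more its non-employed remainder consists of participants with a poor prognosis. Balance at randomisation does not carry over into the strata.

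**4. Direction of the bias for the primary outcome.** This is an illustration only. Assumptions: exponential time to return to work; the protocol's 300 days taken as the control median; one pooled group of everyone on a benefit at 12 months, made up of all non-returners plus returners who lost work again; and job-loss rates that are not in the protocol.

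- Control returned by day 365: 1 − exp(−ln 2 × 365/300) = 0.570.
- SAU, 25% job loss: pool = 0.430 + 0.570 × 0.25 = 0.573, of whom 0.142/0.573 = 24.9% had returned.
- IBBIS-II with no effect on return to work but 12.5% job loss: pool = 0.430 + 0.570 × 0.125 = 0.501, of whom 14.2% had returned. Ratio of cumulative hazards = ln(1 − 0.142)/ln(1 − 0.249) = 0.54, against a true HR of 1.00.
- IBBIS-II with true HR 1.25 and the same 25% job loss: returned 0.652, pool = 0.348 + 0.652 × 0.25 = 0.511, of whom 31.9% had returned. Ratio = ln(1 − 0.319)/ln(1 − 0.249) = 1.34, against a true 1.25.

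Better job retention, which is a benefit, pushes the within-group ratio towards apparent harm. With equal retention the true effect is exaggerated.

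**5. The secondary outcome by stratum.** Table 1 separates unsupported from supported competitive employment. Participants on unemployment benefit or cash benefit, or in a flexjob or subsidised job, at 12 months are essentially outside unsupported employment at 12 months. The expected proportion is near 0% in both arms in those four strata, and the logistic model planned in {20a} has almost no events from which to estimate an odds ratio. SU differs, because a student on SU may also hold a job.

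**The case against.** The strongest reply is that the item is exploratory. {20a} reserves confirmatory status for the primary and secondary questions, the only subgroups with stated power are depression and stress, and the comparisons in all 900 participants do not use this variable. That stands, and it limits the severity. It does not make an uninterpretable comparison interpretable.

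A second reply is that the wording reads like an outcome: a breakdown of where people go after sickness benefit, put in the wrong list. That is possible, and the promised data analysis plan could settle it. As written, however, the list heading makes it a subgroup for every outcome, so the sentence needs the same edit under either reading.

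Third, the claim about the secondary outcome depends on the definition in {18a}. Sample size {14} speaks of employment during the 12-month period, and {20a} of employment at one point in follow-up. If employment at any time counts, benefit status at month 12 does not fix the outcome. A reader might infer that the secondary outcome is zero by definition in every stratum. The documents do not support that, for this reason and because of SU.

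Fourth, a reader might infer from step 4 that the plan would usually report significant harm. Simulating the no-effect case with 25% v 12.5% job loss gives significance against IBBIS-II in about 83% of trials, but only with all benefit types pooled. The plan splits into five. The pooled group has about 64 + 32 = 96 events; divided equally (an assumption), that is about 19 per stratum, and the rate falls to about 28%. At 25% v 20% job loss it is 18% even when pooled. The model also counts everyone in a flexjob or subsidised job as a non-returner or job loser, although the return-to-work definition in {18a} does not exclude supported work. It places every non-returner on a listed benefit, although those still on sickness benefit fit no listed level. The 83% therefore describes no analysis in the plan.

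**Conclusion.** The point holds in a limited form. As written, {20b} plans arm comparisons within groups formed by a consequence of treatment. Those estimates have no causal meaning and may err in either direction. Two things can be stated with some size: the 1.6:1 imbalance (about 180 v 112) in the pool not in employment, which rests on the protocol's 60% v 75%; and a secondary outcome near 0% in four of the five strata, which rests on the {18a} definition. The bias in any one stratum depends on job-loss and benefit rates that the protocol does not give, so no figure should be attached to it. A reader might infer that the trial's main conclusions are at risk. They are not, because the confirmatory comparisons use everyone randomised. This is something that should be fixed before analysis, not a fault that undermines the trial.

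**What to change.** Delete 12-month benefit status from the subgroup list in {20b} and keep only baseline factors as subgroups. Report 12-month status instead as an exploratory outcome by arm: unsupported work, each benefit type, still on sickness benefit, and other. Give differences between arms with 95% confidence intervals and all randomised participants as the denominator. This shows validly whether IBBIS-II changes where people end up after sickness benefit.

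The cost is one sentence in the protocol and a matching entry in the data analysis plan that {20b} promises before the analytic phase. The DREAM records are the same, and neither the sample size nor the data collection changes.

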### Methods in analysis to handle protocol non-adherence and any statistical methods to handle missing data {20c}

The data analyses are based on the intention-to-treat principle. Data from all participants will be included in the analyses, whether they complete the intervention. Incomplete baseline data will be handled using multiple imputation assuming that data is missing at random.

### Plans to give access to the full protocol, participant-level data, and statistical code {31c}

We give access to the full protocol via ClinicalTrials.gov. Access to participant-level data is not applicable due to Danish data protection law.

### Oversight and monitoring

#### Composition of the coordinating center and trial steering committee {5d}

DISCUS has the overall administrative responsibility for the implementation and the operational part of the project. The project is organized with a steering group represented by DISCUS, vocational rehabilitation team members (municipalities), treatment team members (regions), evaluators, and STAR. The steering group meets quarterly to discuss and find solutions to the challenges that may have an impact on whether the project can be carried out as planned and described in the manual and protocol. Deloitte is responsible for data management, randomization, and data collection. The team leaders at the study site are responsible for the day-to-day support for the trial. At CORE, the evaluation is headed by the trial sponsor, who carries the responsibility for the data analysis and evaluation. Metrica are advisors on the design of the evaluation and data analysis.

Deloitte will have authority over data collection. CORE will have authority for the analysis and interpretation of the data, writing of the report and articles, and decision to submit the report and articles for publication. DISCUS, Deloitte, and STAR will not take part in decisions regarding data analysis, nor the interpretation of the publication of results.

